**Figure 1 FIG1:**
[figure not shown]
Study design. The arrows depict the patient flow and the schedule for follow-up visits. Patients diagnosed with triglyceridemia and coronary artery disease are assessed to confirm that their triglyceride levels are 150 mg/dL or higher. Those who meet the inclusion criteria will receive one of the study drugs within one day of randomisation (indicated by the grey arrow). Following drug administration, there is a required follow-up period lasting 12 weeks (shown with a blue arrow). After the 12-week period, patients who provide consent for continued monitoring will enter an extended follow-up phase (indicated by the dotted arrow). During this phase, any modifications to the assigned medication are prohibited. EPA: eicosapentaenoic acid; RHI: reactive hyperemia index

Assessments to be performed during the study period are presented in Table 1. At the baseline, 12 weeks, and 24 weeks, the same data will be collected, while baseline assessments will include demographic data and medication history. Endothelial function will be assessed using RH-PAT (Endo-PAT2000; Itamar Medical, Caesarea, Israel). The follow-up at four weeks will be performed at four weeks for safety monitoring. Safety assessments will include adverse event monitoring and regular laboratory tests for hepatic and renal functions. Medication adherence is monitored by verbal confirmation at the time of the visit. As the RHI is affected by exercise and medication, no major lifestyle changes are allowed during the study period, and changes in medication are prohibited.

**Table 1 TAB1:** Assessments during the study period.

Assessment	Enrollment	Study follow-up period			Discontinuation (at any time)
		4 weeks	12 weeks (±4 weeks)	24 weeks (±4 weeks)	
Medical examination	×	×	×	×	×
Written informed consent	×				×
Clinical symptom	×	×	×	×	×
Adverse events		×	×	×	×
Treatment discontinuation		×	×	×	×
Vital signs	×	×	×	×	×
Blood pressure	×	×	×	×	×
Body weight	×		×	×	×
Laboratory tests	×	×	×	×	×
Reactive hyperemia index	×		×	×	×

RH-PAT

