**Table 2 TAB2:** Primary and secondary outcomes. RHI: reactive hyperemia index; EPA: eicosapentaenoic acid; LDL: low-density lipoprotein; ln: logarithmic

Endpoints	Details
Primary	RHI change after 12 weeks of treatment between the pemafibrate and EPA groups, defined as the difference in logarithmic RHI change calculated as follows: The difference of lnRHI change = ([lnRHI at follow-up - lnRHI at baseline] in the pemafibrate group)-([lnRHI at follow-up - lnRHI at baseline] in the EPA group)
Secondary	1. The difference in RHI change after 24 weeks of treatment between the pemafibrate and EPA groups
	2. Association between RHI and biochemical parameters including triglyceride, LDL-cholesterol, and high-density lipoprotein cholesterol levels, small dense LDL-cholesterol level, high-sensitive C-reactive protein level at baseline and 12 weeks
	3. The differences in change in the following parameters between the pemafibrate and EPA groups: triglyceride, LDL-cholesterol, and high-density lipoprotein cholesterol levels, small dense LDL-cholesterol level, high-sensitivity C-reactive protein level

The primary outcome of the study was to compare the improvement in endothelial function between the pemafibrate and the EPA groups. The secondary outcomes were to assess the change in lipid profiles between the pemafibrate and the EPA groups, to determine correlations between endothelial function and biochemical parameters, and to assess safety.

Further exploratory analysis will include levels of apolipoproteins (apolipoprotein A-I, apolipoprotein B, apolipoprotein C-III, apolipoprotein, remnant-like protein-C), malondialdehyde-modified low-density lipoprotein, interleukin-1β, tumor necrosis factor-α, fibrinogen, urinary 8-hydroxy-2'-deoxyguanosine, and hemoglobin A1c, estimated glomerular filtration rate, and fatty acid fractionation. The exploratory outcomes are hypothesis-generating.

Safety outcomes

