The efficacy analysis will be conducted on the full analysis set (FAS), which comprises all randomised patients who have received one dose of the study drug and undergone at least one follow-up assessment. Patients lacking RHI data or those who discontinue or withdraw from treatment will not be included in the FAS. For any missing values at the 24-week mark, the last observed value for the respective variable will be carried forward (last observation carried forward). Furthermore, a baseline observation carried forward approach will be utilised in the primary outcome analysis. The analysis will be performed based on the intention-to-treat principle, considering patients in their originally assigned treatment groups. Sensitivity analysis will be carried out on data corrected for multiple imputations.

The primary outcome will be evaluated in the FAS using an analysis of covariance (ANCOVA), with a significance level set at α = 0.05, to analyse the ratio of the RHI change rate. RHI has a skewed distribution. Therefore, the logarithmic transformation of RHI is used for analysis. The ratio of the RHI change rate at 12 weeks between the two groups will be assessed. Adjusted covariates will include the assigned treatment (pemafibrate, EPA), age (<median, ≥median), sex (male, female), and baseline TG levels (<median value, ≥median value) as stratified factors of randomisation. Furthermore, the RHI change rate, the ratio of the RHI change rate and 95% CIs will be calculated.

The secondary outcomes, the difference in RHI change at 24 weeks and each lipid parameter at 12 and 24 weeks between the pemafibrate and EPA groups separately, will be analysed using ANCOVA as the primary outcome. The association between changes in RHI and changes in lipid parameter levels at baseline, 12, and 24 weeks will be analysed using Pearson’s analysis.

Prespecified subgroup analyses will be performed on the primary outcome according to the following subgroups: age (<median, ≥median), sex (male, female), baseline TG levels (<median, ≥median), baseline RHI (<median, ≥median), estimated glomerular filtration rate (>60 mL/min/1.73 m^2^, <60 mL/min/1.73 m^2^), body weight (<median, ≥median), hemoglobinA1c (<median, ≥median), presence of current or past smoking. P-values for interaction will not be calculated.

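### The main 24-week analysis fills missing values by LOCF although follow-up past week 12 is optional, so the 24-week RHI and lipid comparisons are pulled towards the 12-week result

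*Protocol article*

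**What the plan says.** The Figure 1 legend of the protocol article separates two periods. Up to week 12, "there is a required follow-up period lasting 12 weeks". Beyond that, "After the 12-week period, patients who provide consent for continued monitoring will enter an extended follow-up phase".

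Table 1 schedules RHI at enrolment, at 12 weeks (±4), at 24 weeks (±4) and at discontinuation, but not at 4 weeks.

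Table 2 lists as the first secondary outcome: "The difference in RHI change after 24 weeks of treatment between the pemafibrate and EPA groups". The Analysis Plan analyses "the difference in RHI change at 24 weeks and each lipid parameter at 12 and 24 weeks" by ANCOVA, in the same way as the primary outcome.

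The Analysis Plan also contains three provisions on missing data and populations that bear on this point:
- The 24-week rule: "For any missing values at the 24-week mark, the last observed value for the respective variable will be carried forward".
- The full analysis set (FAS): "Patients lacking RHI data or those who discontinue or withdraw from treatment will not be included in the FAS".
- A sensitivity analysis using multiple imputation, with no endpoint or time point named.

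**The concern.** LOCF is often criticised on general grounds. Here the objection is more specific, because a missing 24-week value need not come from sporadic dropout. It arises whenever a patient finishes the required 12 weeks and does not consent to go on. That patient's last RHI is the one already used for the primary endpoint, and LOCF enters it again as a 24-week observation.

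The first secondary outcome asks whether the arms differ after 24 weeks of treatment. Under this rule part of the answer is copied from week 12. An effect that has faded would look partly sustained, and one that has grown would be diluted. The copied values also count as new observations in the standard error. Because the rule applies to each variable, the 24-week lipid comparisons are affected in the same way, and so are any 24-week correlations between RHI and lipids that use the filled data.

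**Working it through.** **1. The plan's own figure.** Inputs from Sample Size Calculation: difference in lnRHI 0.076, SD 0.11, two-sided 5%. By the normal approximation, n per arm = 2 × (z₀.₉₇₅ + z_power)² × 0.11² / 0.076².
- 90% power: 2 × (1.960 + 1.282)² × 2.095 = 44.0, giving 45 per arm and 90 in total, as stated.
- 80% power: 2 × (1.960 + 0.842)² × 2.095 = 32.9, giving 33 per arm and 66 in total, as stated.

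These figures are not in dispute. They supply D12 = 0.076 and SD = 0.11 below.

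**2. Which value is carried.** RHI has no scheduled visit between 12 and 24 weeks other than at discontinuation. A 12-week completer who stays in the FAS and does not enter the extension therefore has the 12-week RHI as last observation. With a ±4-week window it was taken at weeks 8 to 16. The 24-week window opens at week 20, so the carried value predates it by at least 4 weeks.

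**3. Effect on the 24-week estimate.** Let q be the share of each arm filled from week 12, and D12 and D24 the true differences. Assume equal q in both arms, and decliners who resemble continuers. Then

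expected LOCF difference = (1 - q) × D24 + q × D12.

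The document gives neither q nor D24, so both are assumptions shown as a range, with D12 = 0.076:

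| q | D24 = 0 | D24 = 0.076 | D24 = 0.114 |
|---|---|---|---|
| 10% | 0.0076 | 0.076 | 0.1102 |
| 20% | 0.0152 | 0.076 | 0.1064 |
| 30% | 0.0228 | 0.076 | 0.1026 |
| 50% | 0.0380 | 0.076 | 0.0950 |

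The middle column shows that the mean difference is unbiased when the two effects are equal.

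**4. Chance of a significant 24-week result when D24 = 0.** With 50 per arm and all values counted as observed, SE = 0.11 × √(2/50) = 0.022. The test statistic is centred at q × 0.076 / 0.022, that is 0.35, 0.69, 1.04 and 1.73 for q = 10%, 20%, 30% and 50%. The probability of two-sided p < 0.05 is then about 6%, 11%, 18% and 41%, against a nominal 5%.

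**5. Copied values as data.** If only observed 24-week values were used, SE = 0.11 × √(2/(50(1 - q))), that is 0.023, 0.025, 0.026 and 0.031 for the same q. LOCF keeps it at 0.022. If the true 12- and 24-week changes have equal variance and correlation ρ, the correlation of the reported changes becomes q + (1 - q)ρ. For an assumed ρ of 0.5 it rises to 0.55, 0.60, 0.65 and 0.75. So even when D24 = D12, the 24-week result is weaker independent evidence of durability than it appears.

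**The case against.** **The FAS may already remove decliners.** The FAS drops patients who discontinue or withdraw from treatment, and the section on discontinuation for individual participants lists a participant's refusal to continue among the criteria. Read together, these could take some decliners out of the FAS. The text does not settle the matter. It does not name 12-week completers who decline optional follow-up, and if all of them were removed the LOCF rule would have little to fill. What stands is that a reader should not infer that everyone who does not continue receives a 12-week value.

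**The carried value need not be the 12-week one.** Table 1 schedules an RHI at discontinuation, so a patient who enters the extension and stops during it could have a later value. It would be wrong to infer that the filled value is always the primary-endpoint measurement. The point is confined to FAS patients who complete week 12 and do not continue.

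**Multiple imputation is already planned.** This is true, and the plan should be credited for it. But it is a sensitivity analysis with no link to the 24-week endpoint, while LOCF is fixed as the 24-week rule.

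**The size rests on assumptions.** This also stands. The only attrition allowance is the step from 90 to 100 participants (10%), which was not set for the extension. At q = 10% the distortion is at most 0.0076 for D24 between 0 and twice D12. A complete loss of effect by week 24 is an extreme case, since changes to assigned medication are prohibited in the extension.

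**Optionality rests on a figure legend.** The body text says "At the baseline, 12 weeks, and 24 weeks, the same data will be collected" and Table 1 lists week 24 as a follow-up visit. Neither statement contradicts the legend, which is explicit that continuing depends on consent.

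**Conclusion.** The point holds for FAS patients who complete week 12 and do not enter the extension. For them, the main 24-week analysis reuses the 12-week RHI and lipid values as if they were 24-week observations. This moves the estimated 24-week difference towards the 12-week one by q × (D12 - D24) and understates its uncertainty.

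With D12 = 0.076 and D24 = 0, the spurious 24-week difference is 0.008 at q = 10% and 0.038, half the planned effect, at q = 50%. These figures assume equal q in both arms and decliners who resemble continuers. The documents give no basis for choosing a value of q, so the upper end of the range is an illustration and not a forecast.

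The consequence is limited to the 24-week secondary analyses. A reader might infer that the primary result is compromised too, but the 24-week LOCF rule does not touch the 12-week comparison or the sample size. The change should be made before the database is closed, and it is not a reason to doubt the primary analysis.

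**What to change.** - Make one of two methods the main 24-week analysis of lnRHI and of each lipid. The first is a likelihood-based repeated-measures model on all observed 12- and 24-week data, with treatment, visit, treatment-by-visit interaction, baseline value and the stratification factors. The second is multiple imputation by arm, which extends a method already planned. Both rely on missingness being explained by the observed data, and the plan should say so.
- Keep LOCF as a sensitivity analysis at most.
- State that 12-week completers who decline the extension remain in the FAS, so that the population rule and the missing-data rule agree.
- Report, per arm, the number who entered the extension and the number with an observed 24-week RHI.

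The change needs no new visits or data, only revised wording in the analysis plan, which the article says is to be completed before the database is closed. The cost is a somewhat wider 24-week confidence interval, which reflects the information actually collected.

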Other exclusion criteria include the use of fibrates or omega-3 fatty acids within 12 weeks prior to informed consent, the use of phosphodiesterase-5 inhibitors, fasting TGs over 500 mg/dL within 12 weeks prior to informed consent, and failure to meet LDL-cholesterol management criteria (>100 mg/dL, based on Japan Atherosclerosis Society Guidelines for Prevention of Atherosclerotic Cardiovascular Diseases 2017) within 12 weeks prior to informed consent. Patients with secondary dyslipidemia, including drug-induced dyslipidemia, or primary dyslipidemia, including familial hypercholesterolemia, are also excluded. Furthermore, exclusion criteria include alcoholism, diabetes mellitus with poor control (hemoglobin A1c >9.5%) or type 1 diabetes mellitus, vasospastic angina and microvascular angina, and a life expectancy of fewer than six months.

Study procedures and randomisation

The flowchart of the study is illustrated in Figure 1. Patients fulfilling all criteria and who will provide written informed consent to participate in this study will be randomly assigned (1:1) to the pemafibrate group (0.1 mg twice daily, with dose adjustments up to 0.2 mg twice daily) or EPA group (900 mg administered two to three times daily). The aim of dose escalation is to achieve a fasting TG level of <150 mg/dL; however, this depends on the patient's response and tolerance. Randomisation will be performed using a computer-generated random sequence web response system by central randomisation. The patients will be stratified by age (<65 years, ≥65 years), sex (male, female), baseline TG levels (<250 mg/dL, ≥250 mg/dL), and baseline RHI (<1.5, ≥1.5).

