No study has investigated the changes in RHI in response to fibrates for hypertriglyceridemia treatment. However, two studies have reported a link between increased TG levels and decreased RHI, with a decrease of approximately 50 mg/dL resulting in a reduction of approximately 0.08 in lnRHI [24,25]. In addition, previous reports have examined changes in FMD, another indicator of endothelial function [15-17,19,26]. Based on these studies, a 10% reduction in TG levels has been estimated to result in a 0.4% increase in FMD. The standard deviation of FMD measurements in multicenter studies is approximately 1.3%. Assuming reductions in TG levels of 45% and 20% for the pemafibrate and EPA groups, respectively, the expected increases in FMD are 1.8% and 0.8%, with a difference of 1.0% between the two groups. When this difference was converted to a logarithmic RHI (lnRHI, as RHI follows a non-normal distribution), the difference in lnRHI between the pemafibrate and EPA groups was estimated to be 0.076, with a standard deviation of 0.11. Assuming a 25% difference in TG reduction between the EPA and the pemafibrate groups in the present study, this would equate to a 50 mg/dL reduction at a baseline of 200 mg/dL, which is in close agreement with the value predicted by the FMD and is reasonable. Using a two-sample t-test with a two-sided significance level of 5% and a statistical power of 90%, the required sample size was calculated to be 90 participants (45 in each group). Considering the possibility of dropouts during the study period, the target number of patients was set at 100 in both groups (50 in each group). Assuming a statistical power of 80%, the number of cases required would be 66, which means that even if more than 10% of cases were to be excluded, the analysis would still be possible.

Analysis Plan

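### The primary ANCOVA leaves out baseline RHI, which is both a stratification factor and the outcome's own baseline: the estimate stays unbiased, but precision is given away

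*Protocol article*

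**What the plan says.** All references are to the protocol article.

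- **Study procedures and randomisation:** four binary stratification factors are named: age, sex, and then "baseline TG levels (<250 mg/dL, ≥250 mg/dL), and baseline RHI (<1.5, ≥1.5".
- **Table 2:** the primary endpoint is a change from baseline, "defined as the difference in logarithmic RHI change calculated as follows": follow-up minus baseline lnRHI in the pemafibrate group, less the same quantity in the EPA group.
- **Analysis Plan:** the primary ANCOVA is specified as "Adjusted covariates will include the assigned treatment (pemafibrate, EPA), age (<median, ≥median), sex (male, female), and baseline TG levels", with TG split at its median. The sentence goes on to identify these covariates as the factors that stratified the randomisation. In that section baseline RHI appears only as a subgroup variable. The 24-week RHI change and the lipid parameters are to be analysed by ANCOVA in the manner of the primary outcome.
- **Sample Size Calculation:** "the difference in lnRHI between the pemafibrate and EPA groups was estimated to be 0.076, with a standard deviation of 0.11". With a two-sample t-test, two-sided 5% and "a statistical power of 90%, the required sample size was calculated to be 90 participants (45 in each group").

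**The concern.** The covariate list does not meet its own stated rationale. It is offered as the set of stratification factors, but it carries three of the four. The one left out is the variable from which the outcome is calculated.

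Two separate costs follow.

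1. A change score tends to be negatively related to its own baseline through regression to the mean. A model without that baseline leaves the variation in the residual.
2. Stratifying on baseline RHI makes the arms more alike on it and so reduces the true sampling variation of the treatment difference. A model that ignores the factor does not credit that reduction. Its standard error is then larger than the true one, the confidence interval is too wide and the test rejects too seldom.

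At stake is the efficiency of the single confirmatory test in a 100-patient superiority trial, and a clear statement of which adjusted model is the primary one.

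**Working it through.** **Inputs from the document.** Difference 0.076; SD 0.11 (the text does not say whether of the change or of a single measurement); two-sided 5%; 1:1 allocation; 45 per arm analysed.

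**Assumed, not in the document.** ρ, the correlation of baseline with 12-week lnRHI, shown from 0.3 to 0.9; equal variances at both times.

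**Step 1: reproduce the plan's figures.** n per arm = 2(z₁+z₂)²(SD/difference)².
- 90% power: 2 × 10.507 × (0.11/0.076)² = 2 × 10.507 × 2.095 = 44.02, so 45 per arm, 90 in all.
- 80% power: 2 × 7.849 × 2.095 = 32.9, so 33 per arm, 66 in all.

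Both stated figures reproduce. Power at 45 per arm is 90.6% by the normal formula and 90.0% by the exact t-test.

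**Step 2: variance with and without the baseline.** With single-time variance s², the change has variance 2s²(1−ρ). After adjustment for baseline the residual variance is s²(1−ρ²). The ratio is (1+ρ)/2, which is below 1 for every ρ below 1.

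**Step 3: put in 0.11 as the SD of change.** Residual SD = 0.11 × √((1+ρ)/2). Required n = 44.02 × (1+ρ)/2, rounded up.

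| ρ | Variance ratio | Residual SD | SE without baseline is wider by | Power at 45 per arm | n per arm for 90% |
|---|---|---|---|---|---|
| no baseline | 1 | 0.110 | – | 90.6% | 45 |
| 0.3 | 0.65 | 0.089 | 24% | 98.2% | 29 |
| 0.5 | 0.75 | 0.095 | 15% | 96.6% | 34 |
| 0.7 | 0.85 | 0.101 | 8.5% | 94.5% | 38 |
| 0.9 | 0.95 | 0.107 | 2.6% | 92.0% | 42 |

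If the true difference were 0.05, power would be 58% without the baseline and 76%, 70% and 65% with it at ρ = 0.3, 0.5 and 0.7.

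**Step 4: is the reported SE right?** This is a different question from Step 3: it compares the model's SE with the actual spread of the estimates. The first simulation had 90 patients, permuted blocks of four within the two RHI strata only, assumed mean RHI 1.6, and 8,000 runs per setting.

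| ρ | Model SE, no baseline | Actual SD | Ratio | Type I error, no baseline | Type I error, with baseline lnRHI |
|---|---|---|---|---|---|
| 0.3 | 0.0231 | 0.0210 | 1.10 | 3.0% | 4.9% |
| 0.5 | 0.0232 | 0.0216 | 1.07 | 3.3% | 4.8% |
| 0.7 | 0.0232 | 0.0220 | 1.05 | 4.2% | 5.3% |

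Simulated power was 91.7%, 91.8% and 90.4% without the baseline, and 97.9%, 96.1% and 93.6% with it.

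The trial stratifies on four binary factors, which gives 2⁴ = 16 cells for about 90 patients, so many blocks stay incomplete and balance on RHI is looser. In simulations of that design (block size and factor prevalences assumed), the SE without baseline RHI was about 3-8% too large and the type I error about 3.5-4.5%. The power gain was essentially unchanged. The two-stratum figures are therefore an upper end.

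**Step 5: the other reading of 0.11.** If 0.11 is the SD of a single measurement, the change has SD 0.11 × √(2(1−ρ)) and the adjusted residual 0.11 × √(1−ρ²). Power at 45 per arm is then 79% without and 93% with the baseline at ρ = 0.3, 85% and 95% at ρ = 0.4, and 90.6% and 96.6% at ρ = 0.5. By ρ = 0.7 both exceed 98%.

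**The case against.** The strongest reply is that nothing here threatens validity. Under randomisation the change-score contrast is unbiased without the baseline. Any leftover imbalance in baseline lnRHI is chance variation, which the standard error already covers. The error is on the conservative side. The trial was sized with an unadjusted t-test, so the 94-98% is power that the design never claimed. All of this stands.

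A reader might infer that the trial is underpowered, or needs 60 rather than 45 per arm. The document does not support that. The 60 is 45/0.75: what a change-score analysis would need at ρ = 0.5 to match the precision of an adjusted analysis with 45. For the planned 90% the relevant comparison is 45 against 34. A shortfall below 90% arises only if 0.11 is a single-time SD and ρ is below about 0.5, and the text settles neither.

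It can also be said that ρ is unknown, and that the article's emphasis on the repeatability of RHI points to higher values, where the gain shrinks. That is fair, and it is why 0.9 is shown.

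Finally, the wording of the covariate list could be read as open-ended, with the rest left to the SAP. For RHI this is weak, because the list is tied to the stratification factors and omits one. For the lipids it carries weight. A reader might infer that every lipid model lacks its own baseline, but a statement that they follow the primary ANCOVA may name only the method and need not fix the covariates.

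**Conclusion.** The inconsistency between the randomisation section and the Analysis Plan is real, and its direction does not depend on the value of ρ as long as ρ is below 1. Its size does. With 0.11 as the SD of change and ρ assumed between 0.3 and 0.7, the omission forgoes a 35% to 15% cut in model variance. That is power of about 90-92% instead of 98-94% at 45 per arm, or equivalently 45 per arm where about 29 to 38 would give 90%. Under the four-factor stratification the test is mildly conservative, with type I error about 3.5-4.5%. At ρ = 0.9 little remains.

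This is a loss of efficiency. It does not bias the estimate or inflate the type I error, and on this reading of 0.11 the planned power is met. It is worth correcting because the correction is free, and because a covariate list that contradicts the stratification leaves room to choose between models after the data are seen.

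**What to change.** - **Primary model:** add continuous baseline lnRHI to the 12-week ANCOVA, optionally with the RHI randomisation stratum (<1.5, ≥1.5). With baseline lnRHI in the model, analysing the follow-up lnRHI or its change gives the same treatment estimate, so the endpoint in Table 2 need not change. The stratum alone would restore the type I error to about 5% but recover less power: 94.6%, 94.1% and 92.0% at ρ = 0.3, 0.5 and 0.7 in the two-stratum simulation.
- **24-week RHI:** use the same covariates.
- **Lipid outcomes:** state that each uses its own continuous baseline, log-transformed where skewed.
- **Sample size text:** say whether 0.11 is the SD of the change or of a single measurement.

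The cost is a line or two in the protocol or SAP. RHI is already measured in everyone at enrolment, and no patients or visits are added. Because the trial is open-label, the change should be dated and made before outcomes are compared by arm; the article already places completion of the SAP before database closure.

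### The primary ANCOVA is said to adjust for the randomisation strata, but only sex matches: age and TG are re-cut at sample medians and baseline RHI is not listed

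*Protocol article*

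**What the plan says.** Under Study procedures and randomisation, the protocol article names four stratification factors, each with a fixed boundary: "The patients will be stratified by age (<65 years, ≥65 years), sex (male, female"), followed by "baseline TG levels (<250 mg/dL, ≥250 mg/dL), and baseline RHI (<1.5, ≥1.5").

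Under Statistical analysis, Analysis Plan, the primary outcome is tested "using an analysis of covariance (ANCOVA), with a significance level set at α = 0.05". The covariates are introduced with "Adjusted covariates will include the assigned treatment (pemafibrate, EPA), age (<median, ≥median), sex (male, female") and end with "baseline TG levels (<median value, ≥median value) as stratified factors of randomisation". Baseline RHI is not in that list. In the same section it appears only among the subgroups, as "baseline RHI (<median, ≥median").

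Table 2 gives the primary endpoint as a between-group contrast, "defined as the difference in logarithmic RHI change". The Analysis Plan applies the same ANCOVA to the 24-week RHI change and to the lipid parameters.

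**The concern.** The document chooses the covariates of its primary model and identifies them as the factors used at randomisation. That identification is wrong for three of the four factors. A median is known only when the sample is complete, so it cannot have been a boundary in the randomisation system.

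Two analysts could therefore follow the same section and fit different primary models, one taking the label at its word and the other taking the listed cut-points. In an open-label trial that choice should be closed before outcomes are seen.

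The RHI omission has the most statistical weight. The endpoint is a change in lnRHI, so the baseline value is part of the outcome and probably the most prognostic of the four factors. If allocation is balanced on a prognostic factor and the model leaves that factor out, the estimate benefits from the balance but the model-based standard error does not reflect it.

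**Working it through.** **1. The two lists side by side**

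| Factor | Randomisation | Primary ANCOVA | Match |
|---|---|---|---|
| Age | 65 years | sample median | no |
| Sex | male, female | male, female | yes |
| Baseline TG | 250 mg/dL | sample median | no |
| Baseline RHI | 1.5 | not listed | no |

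One of four is carried over as defined, two are re-cut and one is absent. The TG boundaries are unlikely to coincide by chance: entry TG runs from 150 to 500 mg/dL, and Sample Size Calculation works from a baseline of 200 mg/dL.

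**2. The plan's own figure**

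Inputs from Sample Size Calculation: difference and SD "estimated to be 0.076, with a standard deviation of 0.11", two-sided 5%, power 90%.

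n per arm = 2 × (1.960 + 1.282)² × (0.11/0.076)² = 44.02, rounded up to 45, so 90 in total. The t-based solution is 45.01 per arm. The stated 90 reproduces. It comes from an unadjusted t-test, so the covariate list does not affect it.

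Unadjusted standard error at 45 per arm: 0.11 × √(2/45) = 0.0232.

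**3. What leaving out baseline RHI does to the standard error**

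Assumptions that the document does not give: correlation ρ between baseline and follow-up lnRHI of 0.3 to 0.7, equal variances at the two visits, normal lnRHI, median RHI 1.6.

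- Share of the variance of change explained by continuous baseline lnRHI: (1 − ρ)/2 = 0.35, 0.25, 0.15 for ρ = 0.3, 0.5, 0.7.
- Baseline SD = 0.11/√(2(1 − ρ)) = 0.093, 0.110, 0.142.
- Cut-point in SD units: c = ln(1.5/1.6)/SD = −0.69, −0.59, −0.45.
- Fraction of that share kept by a split at 1.5: φ(c)²/[p(1 − p)], with p = Φ(c), = 0.53, 0.56, 0.59.
- Standard error with the 1.5 split: 0.0232 × √(1 − share × fraction) = 0.0209, 0.0215, 0.0221.
- Standard error with continuous baseline: 0.0232 × √(1 − share) = 0.0187, 0.0201, 0.0214.

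**4. Simulation**

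Stratified blocks of 4 over the four factors, N=90, SD of change 0.11, effect 0.076, 3,000 runs per scenario. Further assumptions: mean age 68, 80% male, median TG 210 mg/dL, and no link of age, sex or TG with lnRHI.

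| | ρ = 0.3 | ρ = 0.5 | ρ = 0.7 |
|---|---|---|---|
| SE, covariates as listed | 0.0233 | 0.0234 | 0.0233 |
| SE, actual strata | 0.0210 | 0.0216 | 0.0222 |
| SE, strata + continuous lnRHI | 0.0189 | 0.0203 | 0.0215 |
| Type I error, as listed | 0.034 | 0.037 | 0.041 |
| Type I error, actual strata | 0.051 | 0.044 | 0.047 |
| Power, as listed | 0.916 | 0.906 | 0.905 |
| Power, actual strata | 0.947 | 0.938 | 0.920 |
| Power, strata + continuous lnRHI | 0.977 | 0.958 | 0.937 |

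The standard errors agree with step 3. Ratio of listed to actual strata: 0.0233/0.0210 = 1.11 down to 0.0233/0.0222 = 1.05. Power given up against the actual strata: 3.1, 3.2 and 1.5 points. Against strata plus continuous lnRHI: 6.1, 5.2 and 3.2 points. Repeat runs put type I error for the listed model between about 3.4% and 4.3%. The Monte Carlo standard error of a 5% rate at 3,000 runs is √(0.05 × 0.95/3000) = 0.4 points.

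**The case against.** **Power and validity.** Nothing here biases the treatment estimate or raises the false-positive rate, and the listed model still has power of about 0.905-0.916 against a planned 90%. That stands. A reader might infer from the mismatch that the trial is underpowered or its test invalid, and the figures do not support either.

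**Precision.** A reader might also infer that the precision gained by stratifying is lost. Mostly it is not. In a repeat simulation the actual spread of the estimate was 0.0218 for the listed model against 0.0212 for the strata model at ρ = 0.3, and 0.0219 against 0.0217 at ρ = 0.7. What suffers is mainly the reported standard error, which is too wide.

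**Type I error of 3%.** This would follow only from perfect balance at the lowest correlation: 2 × (1 − Φ(1.96 × 1.11)) = 3.0%. With 2 × 2 × 2 × 2 = 16 strata and 90 patients, fewer than 6 per stratum on average, balance is imperfect and the simulated rate is higher.

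**Median cuts.** They are computed from baseline data without reference to outcome, so they cause no bias. They do discard information, but so do cuts at 65 years, 250 mg/dL and 1.5, so this is no argument for one set over the other.

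**An article, with the SAP to follow.** The covariates are said to be included, which could be read as an open list, and a fuller one may properly sit in the SAP. This makes the RHI omission the less certain part. It does not reconcile the age and TG cut-points with the label given to them.

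**Conclusion.** The contradiction holds on the document's own words: three of the four factors described as those of randomisation are either cut differently or not listed. It should be fixed, but it does not threaten the validity of the trial.

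The cost is a conservative and less efficient primary analysis, of the size shown in the working: a reported standard error about 5-11% too large relative to the actual strata, and a few points of power. The whole of that cost comes from the RHI omission and rests on an assumed correlation and an assumed RHI distribution, neither of which the document gives. The effect of re-cutting age and TG cannot be quantified, because their relation to lnRHI is not stated.

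**What to change.** In the Analysis Plan, replace the listed covariates with the factors as randomised: age (<65, ≥65 years), sex, TG (<250, ≥250 mg/dL) and RHI (<1.5, ≥1.5), preferably with continuous baseline lnRHI added. An acceptable alternative is continuous age, log TG and baseline lnRHI with sex, in which case the text should no longer call the set the randomisation factors.

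Use the same model for the 24-week RHI ANCOVA. For the lipid ANCOVAs, use the strata plus the baseline value of the lipid being analysed.

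Fix the choice in the SAP, which the protocol says will be completed before the database is closed. The cost is wording and one or two model degrees of freedom. All the variables are already collected, and the sample size does not change.
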